## Abstract

**Background:**

A personal health record (PHR) is an online application through which individuals can access, manage, and share their health information in a private, secure, and confidential environment. Personal health records empower patients, facilitate collaboration among healthcare professionals, and improve health outcomes. Given these anticipated positive effects, we want to implement a PHR, named MyPregn@ncy, in a Dutch maternity care setting and to evaluate its effects in routine care. This paper presents the study protocol.

**Methods/design:**

The effects of implementing a PHR in maternity care on patients and professionals will be identified in a stepped-wedge, cluster-randomised, controlled trial. The study will be performed in the region of Nijmegen, a Dutch area with an average of 4,500 births a year and more than 230 healthcare professionals involved in maternity care. Data analyses will describe the effects of MyPregn@ncy on health outcomes in maternity care, quality of care from the patients’ perspectives, and collaboration among healthcare professionals. Additionally, a process evaluation of the implementation of MyPregn@ncy will be performed. Data will be collected using data from the Dutch perinatal registry, questionnaires, interviews, and log data.

**Discussion:**

The study is expected to yield new information about the effects, strengths, possibilities, and challenges to the implementation and usage of a PHR in routine maternal care settings. Results may lead to new insights and improvements in the quality of maternal and perinatal care.

**Trial registration:**

Netherlands Trial Register: NTR4063

## Background

Personal health records (PHRs) have been embraced widely in the last decade. PHRs exist in various types, but their shared goal is to be an online application through which individuals can access, manage, and share their health information in a private, secure, and confidential environment. PHRs have been reported to empower patients, to achieve better cooperation among healthcare professionals, and to improve health outcomes [1–4]. The intended benefits of a PHR, which include the achievement of higher standards of care, are welcome in any healthcare setting.

The active involvement of the pregnant woman and better collaboration among the healthcare professionals are explicitly mentioned in the leading Dutch report [5] as components of a strategy to speed up a reduction in Dutch perinatal mortality [6]. Better multidisciplinary collaboration is associated with better quality and outcomes of healthcare delivery [7]. Given the documented positive effects of a PHR and the identified challenges in Dutch maternity care, a PHR in maternity care might be a possible tool to deal with these challenges. Therefore, we will introduce a PHR named MyPregn@ncy. We designed a study to implement MyPregn@ncy in routine maternal care and to evaluate the effects and adoption of MyPregn@ncy by pregnant women and healthcare professionals. We will identify the effects of MyPregn@ncy on the health outcomes in maternity care, quality of care from patients’ perspectives, and collaboration among healthcare professionals. Additionally, we will focus on the process of implementation of this innovative and complex intervention. We hypothesise that the introduction of a PHR for pregnant women improves health outcomes, positively influences the quality of care from patients’ perspectives, and enhances collaboration among healthcare professionals. We believe it is feasible to implement such an apocalyptical PHR in Dutch maternity care, which will eventually lead to the improvement of maternal and perinatal care.

The aim of this paper is to present an overview of the study. We describe the development of the tool MyPregn@ncy, the design of the study, and the specific aspects of evaluation.

## Methods/design

### Setting

In Dutch maternity care, different healthcare professionals are involved with a pregnant woman and her (unborn) child [8]. Community-based midwives, maternity care assistants, youth health physicians, and nurses provide primary care. Obstetricians, obstetricians in training, hospital-based midwives, and paediatricians provide secondary and tertiary care. Community-based midwives are qualified to provide full prenatal and perinatal care to all women with uncomplicated pregnancies and childbirths. In case of risk factors or complications, women are referred to secondary or tertiary care [9]. Tertiary care takes place in centres for perinatology with a neonatal intensive care unit and an obstetric ‘high-care’ department.

The hospital-based midwife is supervised by the obstetrician (in training) and attends approximately one-half of the births in secondary/tertiary care [10]. The maternity care assistant supports the community-based midwife during childbirth and subsequently takes care of the mother and child up to day 10 postpartum at the home of the new-born. She reports essential health information to the community-based midwife, who is responsible for medical care. Afterwards, the youth health department takes over the care for the baby, with the support of specialised doctors and nurses.

In 2014, 86 % of all pregnant women started their maternity care in a primary care setting. Of these women, 51 % started and 29 % eventually completed birth in a primary care setting [10]. After birth, the medical care is under the supervision of a community-based midwife, and 96 % of all women later receive care from a maternity care assistant at home [10]. Overall, the Dutch system involves a number of referrals during pregnancy, during birth, and after birth.

Healthcare professionals in maternity care work in a regional multidisciplinary collaborative organization situated around a hospital or city, in which they create joint protocols and make distinct appointments for referrals in (acute) care.

### Study population

The study will be performed in one regional collaborative organisation in the area of Nijmegen, a Dutch region with an average of 4,500 births a year and more than 230 healthcare professionals involved in maternity care. Community-based midwives are employed in one of 11 independent practices, whereas hospital-based midwives, obstetricians (in training), and paediatricians work in two different hospitals (one providing secondary care and one providing secondary and tertiary care). Maternity care assistants are employed by one organisation and youth health doctors and nurses are employed by one of 14 offices, all of which are coordinated by one organisation.

Each pregnant woman, independently of the gestational age and care setting, will be invited to participate in this study individually; that is, she will be offered the possibility to start her PHR (MyPregn@ncy). All healthcare professionals in the area will be informed of and requested to actively participate in the study.

### Ethical approval

The medical ethical committee of the Radboud University Medical Centre has awarded full ethical approval for this project (CMO No. 2011/381). The study is registered at the Dutch Trial Register (NTR4063).

### Study design

The effects of the implementation of a PHR in maternity care on patients and professionals will be identified in a stepped-wedge, cluster-randomised, controlled trial. This type of trial is suitable for studying the effects of a new intervention, which is implemented at the cluster level, but experienced and measured by its impact on individuals [11, 12]. In essence, a stepped-wedge trial randomly allocates clusters to groups that crossover from a control condition to an intervention at different crossover points. In the present study, all healthcare professionals, working at 13 sites (11 community-based midwife practices and two hospitals, comparable in the number of patients) agreed to participate. Following baseline measurements, sites will be randomly assigned to four groups, containing three or four sites. The two hospitals are randomly allocated to group 1 and group 2; groups 3 and 4 contained only community-based midwife practices. The length of time between the two successive crossover points is 3 months. The total trial duration is 21 months. Figure 1 illustrates the study over time, including a pre-rollout period, four crossover points, and a post-rollout period. At the start of the study, all sites belong to the control group; at the end of the study, all sites belong to the intervention group. Data collection will be performed in all steps along the trial, coinciding with all four crossover moments.

**Fig. 1 Fig1:**
[figure not shown]
Schematic overview of the study process

### Outcome measures

The primary outcome measure in this study is health outcomes in maternity care. We will use a composite maternal/neonatal outcome measure: the total proportion of uncomplicated pregnancies/births. This includes the following conditions: gestational age at time of delivery is 37–41 weeks, spontaneous start of contractions, spontaneous rupture of membranes, no help during delivery, weight of neonate 5–95 %, APGAR score after 5 min > 7, and no serious postpartum haemorrhage.

Secondary outcome measures are the quality of care from the patients’ perspectives, collaboration among healthcare professionals, and the adoption of MyPregn@ncy by patients and professionals.

### Intervention

The intervention in the present study is the implementation of a PHR, named MyPregn@ncy, for each pregnant woman and her healthcare professionals. MyPregn@ncy is provided by www.mijnzorgnet.nl. The initial PHRs facilitated by MijnZorgnet have recently been used for women experiencing infertility and persons with Parkinson’s disease [13]. The use of a PHR in a maternity care setting is new in the Netherlands.

To ensure safe access to MyPregn@ncy, pregnant women register and log in using their personal DigiD, an identification code provided by the Dutch government. Healthcare professionals register and log in with their personal professional national electronic identification or with a username and password.

Once registered on the website, the pregnant woman owns the PHR. She decides who is granted access to her PHR and, therefore, is a member of her personal care team. She can invite all people (e.g. healthcare professionals and partner/relatives) she considers to be important for her health and for the care process during her pregnancy and birth.

Functionalities of the PHR MyPregn@ncy include the following: (1) communication with one or more care team members, (2) a diary (blogging feature), (3) a library (storage of important documents), and (4) interactive (medical) modules specifically developed for pregnant women. All team members in one PHR can access all fields in the PHR and can add, act, or react. All activities are logged, so the owner has full insight into all delivered input.

In addition to the PHR, the informational website www.mijnzwangerschap.org will be launched to support the introduction and use of MyPregn@ncy and the accompanying study.

To test the developed prototype of the PHR and design of the implementation strategy, we organised eight focus groups. Participants (n = 41) were recommended patient representatives from 16 hospitals and healthcare organisations across the Netherlands. A focus group interview guide was developed in conjunction with other researchers to ensure objectivity. Participants discussed when they would join a PHR, what was unclear about the PHR, what frightened them, and when a PHR had additional value to standard care. Focus groups were audiotaped and transcribed verbatim. Transcripts were read several times and analysed. The model of Cabana et al. [14] was used to analyse all focus group discussions in a systematic way. We categorised and identified six major themes from the focus group data: patient empowerment, safety and access, communication, culture change, legal aspects, and organisation. The results indicated that the information on the PHR must be secure and easy to use and that additional value lies in patient empowerment and online communication. Participants expressed concerns about accessibility for all patients (language and writing problems) and legal aspects (liability and privacy law). Overall, the message resulting from the focus groups showed that a PHR for pregnant women has value but must be a tool next to regular care instead of a replacement of care. Thanks to the input of the focus groups, we learned about barriers to and facilitators of a PHR and designed our communication about the study and the implementation strategy.

### Implementation strategy

MyPregn@ncy will be offered to the pregnant woman by the midwife practices or obstetrics clinics, depending on where she receives her care. To successfully offer the PHR, all healthcare professionals must indeed inform the pregnant woman about MyPregn@ncy, they must understand the use and possibilities of MyPregn@ncy (so that they can explain it correctly), and that they must have their own profile on www.mijnzorgnet.nl (so they can actively participate in MyPregn@ncy with the pregnant woman). To achieve optimal preparation and propagation of the tool, we will create various information leaflets and an informational and supporting website, www.mijnzwangerschap.org. Furthermore, we will visit each participating midwife practice and obstetric clinic to explain MyPregn@ncy and the study design.

In addition to the face-to-face information from their healthcare professionals, pregnant women will be informed of the PHR by local newspapers and by a short movie on digital information screens in the practices and clinics.

During all communication, it will be stated explicitly that the present implementation will be studied and evaluated. It will be emphasised that, at all times, researchers will not have the ability to directly access the PHR. Informed consent will be obtained from each participant. During the study, researchers will be available for questions and clarification for both pregnant women and healthcare professionals. Finally, involved healthcare professionals will regularly receive newsletters on the progress of the study.

### Measurements

Table 1 presents an overview of all measurements used.

**Table 1 Tab1:** Overview of outcome measures with accompanying methods and measurements

Outcome measure	Study population	Method	Instrument	Time of measurement
Healthcare	All pregnant women in care in the area	Database	Perinatal Data Register	Five times, along all successive steps of the study
Quality of care	All pregnant women in care in the area	Survey	Questionnaire ReproQ	Five times, along all successive steps of the study
Collaboration	All maternity care healthcare professionals in the area	Survey	Social Network Analysis	Baseline and one post measurement
Adoption	All users of MyPregn@ncy	Log format, Survey, Interview	Log data, Questionnaire, Topic list	During and after implementation

The total proportion of uncomplicated pregnancies/births will be based on data from the Dutch Perinatal Registry (PRN). In the Netherlands, more than 95 % of all births and accompanying perinatal outcomes are centrally registered in this large national database [10].

The quality of care from the patients’ perspectives will be measured by an adapted version of the questionnaire ReproQ [15]. This new questionnaire has been developed to evaluate the whole maternity care, regardless of where the care is given [15, 16]. Development of this self-report questionnaire has been based on the 8-domain WHO Responsiveness model, including the following domains: dignity, autonomy, confidentiality, communication, prompt attention, social consideration, basic amenities, and choice and continuity [17]. The original questionnaire consists of two parts with largely identical questions: an antepartum questionnaire and a postpartum questionnaire. Due to considerations of time and response, we will use a combined version of both questionnaires in the present study, 6 to 10 weeks postpartum. Subgroups of participants in the study groups will be invited to complete the ReproQ in every phase of the stepped-wedge design. The results of the questionnaires will be calculated in domain scores and overall scores, ranging from one to four [15]. PRN data and ReproQ data will be collected during each step of the stepped-wedge study.

Collaboration between healthcare professionals in maternity care will be measured using Social Network Analysis (SNA). SNA is a quantitative methodology that measures and analyses connections between healthcare professionals in patient care [18]. It combines the concept of the sociogram (a visual representation of relationships in a social group) with elements of graph theory to analyse patterns of interaction among people in networks [18]. We will measure SNA two times in this study: a baseline measurement before the start of the intervention and one post measurement at the end of the study. Therefore, all healthcare professionals in maternity care in the area will be digitally invited for SNA. They will be asked to indicate with whom of their colleagues they had medically oriented contact concerning at least one patient in the last 6 months. The results will be illustrated in a sociogram, and various key network measures will be calculated, such as the number of contacts and centrality of each profession [19]. Finally, the adoption of MyPregn@ncy will be determined by a process evaluation during and after the implementation, according to Hulscher et al. [20]. This process evaluation will provide insight into the usage and appreciation of the various elements of the PHR by the pregnant women and their healthcare professionals. Barriers and facilitators to the use of MyPregn@ncy will be determined, using the theoretical framework of Cabana et al. [14]. Information will be gathered through semi-structured telephone and face-to-face interviews, and questionnaires. Log data will be used to measure the number of accounts and the number of logins per person. Qualitatively, we will conduct interviews based on a topic list with patients and healthcare professionals on their experiences with the intervention, including their perceptions of its utility, convenience, barriers, and facilitators to implementation, and options on long-term sustainability.

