### Statistics

Sample size calculations have been based on an expected improvement of 47 % to 60 % in the proportion of uncomplicated births. Combined with an alpha of 0.05, 80 % power, and a design effect (correction factor due to a stepped-wedge design [21]) of 0.62, a total of 305 pregnant women is necessary for each step. With 13 sites and an expected uptake rate of 25 %, 84 pregnant women/step/site are needed to measure the effects.

Data analysis for the stepped-wedge design will be performed according to an intention-to-treat protocol at the end of the study period, once all sites have at least completed one 3-month intervention period. Individual PRN and ReproQ data will be combined with the different sites. To estimate the intervention effect on the outcome measures, a standard mixed-model approach will be used. The mixed model will incorporate fixed terms for intervention (before versus after), time (3-month period), as well as a correlation of repeated measurements over time as random effects. Hence, the analyses will have the element of a time-series analysis with multiple time points before and after the intervention. Analyses will be performed using SPSS (version 20.0 for Windows: SPSS Inc., Chicago, IL, USA).

Description of the network data by Social Network Analysis (SNA) involves visual analysis of network diagrams produced using a specific software program, NetDraw [22]. This software converts matrices of network data into diagrams and individual nodes using complex algorithms. We will use UNICET v6 [19] to construct the network and obtain network parameters and SPSS 20 (SPSS Inc., Chicago, IL, USA) for statistical analysis.

In addition to log data analysis, the interviews will be audiotaped and transcribed verbatim. The interviews will be independently coded by two persons based on the topic list.

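### Collaboration is surveyed only before rollout and after full rollout, so the stepped-wedge design cannot separate an effect of the record on it from calendar time

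*Protocol article*

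**What the plan says.** Study design states that effects "on patients and professionals will be identified in a stepped-wedge, cluster-randomised, controlled trial". It describes 13 sites in four groups of three or four, crossing over 3 months apart, and adds that data are collected at every step. It also fixes the state of the sites at both ends: "At the start of the study, all sites belong to the control group", and "at the end of the study, all sites belong to the intervention group".

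For collaboration, Measurements departs from data collection at every step. Table 1 gives "Baseline and one post measurement", against five measurements for the registry data and ReproQ. The text below the table confirms it: "a baseline measurement before the start of the intervention and one post measurement at the end of the study". Each professional is asked about "medically oriented contact concerning at least one patient in the last 6 months".

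The Background hypothesises that the record strengthens collaboration, and the Abstract says the analyses will describe its effects on collaboration. Statistics names only registry and ReproQ data in the stepped-wedge paragraph. Network data get a separate paragraph on diagrams and network parameters, with an unspecified analysis in SPSS. The limitations in the Discussion cover step length and the allocation of the hospitals, but not the two-wave measurement of collaboration.

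**The concern.** A stepped-wedge trial separates the intervention from time because, at intermediate measurements, some sites have crossed over and others have not. An outcome measured only before the first crossover and after the last never meets that situation. The order of crossover is randomised, but no collaboration measurement makes use of it as a concurrent comparison.

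The claim about professionals rests on this outcome. The registry and ReproQ outcomes concern patients, and adoption is recorded among users during and after implementation, so it has no control measurement. If collaboration carries no stepped-wedge contrast, the statement in Study design has no outcome on the professional side to support it.

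Confounding by time is plausible. The Background itself reports that better collaboration is part of a national strategy to reduce perinatal mortality, so change could occur over a 21-month study without the record. At stake is a causal reading of a secondary outcome that the data could not support.

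**Working it through.** The protocol gives no sample size or effect figure for collaboration, so there is none to reproduce. The check is whether the effect can be estimated at all.

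**Inputs.** 13 sites in four groups of three or four, which forces sizes 4, 3, 3 and 3 (Study design); one crossover per 3-month step (Study design); five measurement times for registry and ReproQ, two for collaboration (Table 1); fixed terms for intervention and 3-month period (Statistics). Assumptions: the group of four crosses first, and sites enter as fixed effects.

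**Model.** For site i at wave j: outcome = site(i) + period(j) + θ·X(ij), where X = 1 once the site has crossed over. θ is estimable only if X is not a linear combination of the site and period columns.

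| Schedule | Columns | Rank | Residual sum of squares of X given site and period |
|---|---|---|---|
| Five waves | 13 + 4 + 1 = 18 | 18 | 4.89 |
| Baseline and end only | 13 + 1 + 1 = 15 | 14 | 0 |

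With two waves, X is 0 for all 13 sites at wave 1 and 1 for all 13 at wave 2, which is the period indicator itself. Only the sum of θ and the period effect can be estimated. Dropping the site effects does not help: 3 columns, rank 2. This holds whichever group has four sites and however many professionals respond.

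**Look-back.** Let m be the months from the fourth crossover to the second survey. The control share of group 4's window is max(0, (6 − m)/6).

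- m = 3: 3/6 = 50 %.
- m = 6 or more: 0 %.

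Four crossovers 3 months apart span 3 × 3 = 9 months. That leaves 21 − 9 = 12 months for the pre-rollout and post-rollout periods together. An even split would give m = 6 and a share of 0 %. The actual split is not in the text, and Figure 1 is not shown. The 50 % end assumes that the survey comes no earlier than 3 months after the fourth crossover. Group 4 is three or four of the 13 sites.

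**The case against.** The strongest reply is that the protocol already keeps collaboration out of the stepped-wedge analysis. Table 1 shows the different schedule openly, and Statistics speaks of describing the network data. On that reading, only a broad sentence in Study design is loose. The observation about Statistics is correct, but it does not withdraw the claim in Study design or the hypothesis in the Background, and the Discussion does not tell the reader that this outcome is uncontrolled.

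A reader might go further in four directions that the document does not support.

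- **The second survey mixes control and intervention time.** The 3-month minimum, "once all sites have at least completed one 3-month intervention period", says when the stepped-wedge analysis may run. It does not date the network survey, which is placed at the end of the study. The post-rollout period may already be long enough.
- **The design holds no randomised information on collaboration.** That is true only of the on/off term. At the end, groups differ in exposure by up to 3 × 3 = 9 months, and a duration term is estimable (rank 15 of 15). No such analysis is planned, the hospitals are confined to groups 1 and 2, and network ties run across groups, so it would not rescue the on/off effect.
- **Any regional trend will be reported as an effect.** The protocol does not say how the network result will be interpreted and documents no trend in this region.
- **A survey during rollout is the obvious cure.** A wave halfway through makes the on/off term estimable on paper (16 columns, rank 16, residual sum of squares 2.15). But between the second and third crossovers group 1 has 3 to 6 months of exposure and group 2 has 0 to 3, so 0 to 50 % and 50 to 100 % of their 6-month windows would be control time. Both hospitals would sit on one side of a comparison of groups 1 and 2 with groups 3 and 4, and ties link professionals in different conditions. Maternity care assistants and youth health staff belong to none of the 13 randomised sites. One regional before-after map is a defensible choice, provided it is labelled as such.

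**Conclusion.** The point holds as a mismatch between claim and design. With one survey when all 13 sites are control and one when all are intervention, the on/off effect of the record on collaboration is completely confounded with calendar time (rank 14 of 15). More respondents or a different analysis of the same two waves would not recover it. This rests only on the schedule in Measurements and the site states in Study design.

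The look-back point is conditional: between 0 and 50 % of group 4's window is control time if at least 3 months have passed since the fourth crossover, and none if at least 6 have.

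The consequence is limited to one secondary outcome. The registry and ReproQ outcomes, including the primary, keep their five measurements and their stepped-wedge contrast.

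**What to change.** 1. In Study design, restrict the statement on effects identified by the stepped-wedge trial to the registry and ReproQ outcomes, and limit the remark on data collection at every step in the same way.
2. In Statistics, state that collaboration is an uncontrolled, descriptive before-after comparison and that a change between the two surveys cannot be attributed to the record.
3. In the Discussion, add this to the limitations.
4. Confirm that the second network survey falls at least 6 months after the fourth crossover. If it does, state the date; if not, move it or report the control share of group 4's window.

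An added survey during rollout is not recommended, for the reasons given above.

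The cost is a few sentences and possibly a later survey date. The downside is a weaker claim for one secondary outcome, which is the claim that the two surveys can support.
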